### Study procedures

The baseline study visit lasts about two hours and includes interview of both spouses' demographic data, diagnoses, medications used, and baseline use of health and social services. The diagnoses and medications are confirmed from medical records provided by the couples. Charlson comorbidity index is calculated to assess the severity and prognostic value of the participants' disease burden [14].

The AD patients are assessed by Clinical Dementia Rating Scale (CDR) [15], Minimental State Examination (MMSE) [16], verbal flow [17,18], clock drawing test [19], Mininutritional Assessment (MNA) [20], Neuropsychiatric Inventory (NPI) [21,22], Cornell depression test [23], mobility tests and balance tests [24], and the Functional Independence Measure (FIM) [25]. Patients' weight, blood pressure (with 10 min rest and recorded in a sitting position), heart rate and handgrip strength [26] are assessed on each visit. Falls and fractures are recorded with the aid of diaries kept by caregivers and recorded on each visit.

The spousal caregivers are assessed by the Zarit burden scale [27], Geriatric Depression Scale (GDS) [28], RAND36 [29,30] and mobility and balance tests [24]. At six months the caregivers are asked to give feedback for the study and their satisfaction is assessed.

The couples are randomized in clusters of 30. After assessing 30 couples with eligibility and frailty criteria confirmed and agreeing to consent the study, the randomization is performed. Couples are randomly allocated by means of computer-generated random numbers to three arms: to receive home rehabilitation, day care rehabilitation or to receive the usual care. The study nurse calls by telephone to a randomization staff member who has not seen the couples neither their clinical records. She assigns the next number from the computer and the group assignment to the patient.

Participating couples are assessed by two study nurses four times during the year: at baseline, and at 3, 6, and 12 months. In addition, those remaining in the community will be invited for a follow-up visit at 24 months. The study assessment procedures are described in table 1. Use of health and social services, institutionalizations and death dates on both the patients and the caregivers will be retrieved from the central registers until two years from baseline measurements.

**Table 1 T1:** Study assessment procedures and timetable.

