### Outcome measurements

Primary outcome measures are changes in patients' mobility assessed by the tests described by Guralnik et al [24] and in physical functioning according to the FIM measure [25].

Secondary outcome measures are changes in patients' cognition by verbal flow [17] and MMSE [16], neuropsychiatric symptoms by NPI [21,22] and Cornell [23], number of falls, and permanent institutionalizations and time spent at home. Changes in caregivers' satisfaction, burden by the Zarit burden scale [27], depression by the GDS [28], health-related quality of life by the RAND-36 [29,30] will be measured as secondary outcomes.

Total mortality, use and costs of health and social care services of both spouses as well as cost-effectiveness of the intervention will be measured up to 24 months from the beginning of the baseline measurements.

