### Statistical analyses

Sample size was calculated based on the FIM measure [25]. With an estimated standard deviation 20, and type I error 5%, 80% power, 63 patients would be needed in each group to show a 10-point difference between groups. With estimated 10% drop outs in each group about 70 patients are needed in each group. Data will be analyzed on intention-to-treat basis. Imputation method "the last observation carried forward" (LOCF) and "Worst-rank score"-principle will be used.

In these baseline findings, for the continuous variables, descriptive values were expressed by means with standard deviations (SD) and medians with range. For the variables with a normal (Gaussian) distribution, statistical comparisons between the groups are made by using an analysis of variance. If the variables have a non-normal distribution or ordinal level, statistical comparison between groups was made using the Kruskall-Wallis test. Measures with a discrete distribution were expressed as percentages (%) and analysed by Chi-Square or Fischer's exact test when appropriate.

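### The study nurse role requests each allocation and study nurses then assess FIM and mobility at follow-up, with no stated separation, so assessor blinding is unprotected

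*Protocol article*

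**What the plan says.** All of this is in the protocol article.

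- **Timing (Study procedures).** Randomization follows the baseline assessment of a batch of couples: "After assessing 30 couples with eligibility and frailty criteria confirmed and agreeing to consent the study, the randomization is performed".
- **Who asks for the allocation (Study procedures).** "The study nurse calls by telephone to a randomization staff member who has not seen the couples neither their clinical records". The next sentence reads "She assigns the next number from the computer and the group assignment to the patient".
- **Who assesses (Study procedures).** "Participating couples are assessed by two study nurses four times during the year: at baseline, and at 3, 6, and 12 months". No other assessor is named.
- **What is assessed.** Outcome measurements gives the primary outcomes as change in mobility ("Primary outcome measures are changes in patients' mobility assessed by the tests described by Guralnik et al") and change in physical functioning on the FIM. Table 1 schedules both at baseline and at 3, 6, 12 and 24 months.
- **Other data sources (Study procedures).** "Use of health and social services, institutionalizations and death dates on both the patients and the caregivers will be retrieved from the central registers". For falls: "Falls and fractures are recorded with the aid of diaries kept by caregivers and recorded on each visit".

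The article does not describe the assessors as blinded, and it does not describe them as unblinded.

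**The concern.** The patient and spouse know whether they receive home visits, day-centre sessions or usual care, so they cannot be blinded. For outcomes that a person measures or rates, the main protection left is an assessor who does not know the arm. The described procedure sends the request for allocation through the same staff role that later assesses both primary outcomes. If the caller learns the arm and then assesses that couple, expectation can enter the FIM ratings and the conduct of the mobility tests. The analysis cannot remove such a bias afterwards, because it looks the same as a treatment effect. It would affect the outcomes on which the trial's main conclusion rests.

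**Working it through.** **1. The procedure step by step**

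| Step | Who, as stated | Exposed to knowledge of arm? |
|---|---|---|
| Baseline FIM and mobility | Study nurses | No: taken before randomization |
| Request for allocation | The study nurse, by telephone | This is the point of exposure |
| Issue of number and group | Staff member who has not seen couples or records | Concealment before assignment is protected |
| FIM and mobility at 3, 6, 12 months | Two study nurses | Yes, if the caller learns the arm and assesses |
| Secondary outcomes assessed by the nurses after baseline | Two study nurses | Yes, on the same condition |
| Service use, institutionalization, death | Central registers | Not through the nurses' rating |
| Falls | Caregiver diaries, recorded at visits | Not in the same way; the caregiver knows the arm whoever telephones |

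With two nurses named as assessors and the caller described as the study nurse, the caller is probably one of the two. The usual reason for such a call is to learn the assignment. Both steps are inferences; the text states neither outright.

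**2. The plan's own figure**

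Inputs from Statistical analyses: SD 20, difference 10 points, type I error 5% (taken as two-sided, which reproduces the stated number), power 80%.

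n per arm = 2 × (1.960 + 0.842)² × 20² / 10² = 62.8, so 63, as stated ("With an estimated standard deviation 20, and type I error 5%, 80% power, 63 patients would be needed in each group"). With 10% dropout, 63 / 0.90 = 70 per arm, and 3 × 70 = 210. The plan's figures reproduce. They are used here only to set a scale.

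**3. Illustration of what a rating shift would do**

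Assumptions, none of them in the document: no true effect, and one active arm rated b FIM points higher than control by a constant shift.

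Standard error of the difference = 20 × √(2/63) = 3.563.

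False-positive rate = [1 − Φ(1.960 − b/SE)] + Φ(−1.960 − b/SE).

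| b (points) | b/SE | Upper tail | Lower tail | Total |
|---|---|---|---|---|
| 0 | 0 | 0.025 | 0.025 | 5.0% |
| 1 | 0.281 | 0.047 | 0.013 | 5.9% |
| 2 | 0.561 | 0.081 | 0.006 | 8.7% |
| 3 | 0.842 | 0.132 | 0.003 | 13.4% |
| 4 | 1.122 | 0.201 | 0.001 | 20.2% |

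The noncentral t version (124 degrees of freedom) gives 5.9%, 8.6%, 13.3% and 20.0%. Rounded, both give about 6%, 9%, 13% and 20%. For scale, 2 points is 2/20 = 0.1 SD, or one fifth of the 10-point design difference. No similar figure can be given for mobility, because the article states no SD for it.

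**The case against.** The strongest reply is that the central facts are inferred. The article refers to one study nurse in the allocation sentence and two in the assessment sentence. It does not say that the caller is one of the two, is told the group, or sees that couple again. The sentence on issuing the assignment names the patient as its recipient. A journal article condenses the full protocol, no blinding claim is made that could be contradicted, and a missing blinding statement would not be a finding by itself.

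Much of this stands. A reader might infer that the procedure itself unblinds the assessors. The document does not support that, since one nurse could call and the other assess, or the group could go straight to the couple. A reader might also infer that the nurses measure every outcome. They do not: service use, institutionalization and deaths come from registers, falls come from diaries, and baseline values precede allocation. A bias in favour of the active arms is the expected direction, not a demonstrated one. The documents also give no ground for a shift of any particular size, or for treating FIM and mobility as equally open to the assessor's influence.

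The objection does not dispose of the conduct step. The article chose to describe the allocation route in some detail, and that route runs through the assessing role. Staff could follow it exactly as written and leave the follow-up primary outcomes open to an assessor who knows the arm. A statistical analysis plan could not correct that later.

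**Conclusion.** The point holds as a cheap improvement to a stated procedure; it does not show that blinding was broken. The study nurse role requests the allocation and study nurses assess FIM and mobility after baseline, with no stated separation. Assessor blinding of those outcomes, and of secondary outcomes the nurses assess at follow-up, is therefore unprotected. Concealment before assignment is sound.

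The size of any bias is unknown. Under the assumed shifts of 1 to 4 FIM points, the false-positive rate of a single contrast would lie between about 6% and 20% instead of 5%. This rests on a constant shift between arms, the plan's SD of 20 and 63 patients analysed per arm. It shows sensitivity and is not an estimate for this trial.

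**What to change.** Change the procedure in one of two ways:

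1. The randomization staff member, or other existing staff who do not assess, passes the assignment to the couple and the rehabilitation providers, and not to the assessing nurses. Since the randomization staff member has so far been kept apart from the couples, this contact should come only after assignment.
2. If a nurse must make the call, the other nurse does that couple's follow-up FIM and mobility tests. This requires visits to be organised so that one nurse can do those tests alone.

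With either option, ask couples not to disclose their arm, put service-use questions after the primary tests at each visit, and record the assessor's guess of arm at 12 months. If neither option is workable, state that the assessments are open and list this as a limitation.

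The cost is a change of procedure wording and some scheduling, with no new staff. Some accidental unblinding will remain, because couples may reveal their arm; the recorded guesses would help to show how much.

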**AD patient**						
Inclusion criteria	X					
Demographics, diagnoses, drugs		X				
CDR		X				X
MMSE		X			X	X
Verbal flow, clock drawing test		X	X	X	X	X
MNA		X				
Weight, BMI		X	X	X	X	X
Mobility and balance tests by Guralnik		X	X	X	X	X
FIM		X	X	X	X	X
NPI		X		X		
Grip strength, blood pressure, heart rate		X	X	X	X	X
Cornell depression scale		X			X	
Falls and fractures			X	X	X	X
Use of health and social services, admission to permanent institutional care, mortality			X	X	X	X
Spousal caregiver						
Demographics, diagnoses, drugs		X				
Zarit burden scale		X			X	X
GDS		X			X	
RAND-36 QOL		X			X	X
Mobility and balance tests by Guralnik		X			X	
Use of health and social services, mortality			X	X	X	X

^1 ^CDR = Clinical dementia Rating Scale (Hughes et al 1982) (0.5 suggests possible dementia, 1 mild, 2 moderate, and 3 severe dementia); MMSE = Minimental State Examination (Folstein et al. 1972); MNA = Mininutritional Assessment (Guigoz et al. 2002) (< 24 suggests risk for malnutrition or malnourishment); BMI = Body mass index; Guralnik's mobility tests (Guralnik et al. 1994); FIM = Measure of functioning (Pollak et al. 1996); NPI = Neuropsychiatric inventory (Cummings et al. 1994, 1997); Cornell = depression test (Alexopoulos et al. 1988); Zarit burden scale (Zarit et al. 1980), GDS = Geriatric depression scale (Yesavage et al. 1982-3); RAND-36 = Measure of health related quality of life (Parker et al. 2006)

The flow chart of the study is described in figure 1.

**Figure 1 F1:**
[figure not shown]
**Flow chart of the study**.

### Intervention

A total of 210 patients will be randomized in three groups (70 per each arm) as follows:

#### Intervention

A geriatrician performs comprehensive geriatric assessment prior the intervention and makes the rehabilitation plan including also nutritional care.

1. Home-based physical exercise and rehabilitation procedures (one hour twice a week for 12 months) are performed by physiotherapy professionals of an expert organization (Suomen Fysiogeriatria), with long-term experience of dementia exercise rehabilitation. Interventions are tailored according to the patient's and caregiver's needs (for example: training transfers, stair climbing, balance training, executive functioning or dual-tasking).

2. Day rehabilitation centre-based physical exercise and rehabilitation (4 hours twice a week for 12 months) is organized and performed by professionals of dementia physiotherapy at two day rehabilitation centres (with gym and experience) performing the day care rehabilitation. Intervention consists of endurance, balance, and strength training as well as dual task training and exercises directed to improve executive functioning. Taxi transportation and lunch are provided for participants during the intervention days.

The intervention is provided up to one year or until patient is admitted to permanent institutional care.

Patients randomized to the control group receive the usual care in normal health care system, but they are provided with oral and written advice on nutrition and exercise by the study organization.

As a nutritional advice, all patients receive advice to ensure a sufficient intake of energy and protein [4] and to take 20 μg of vitamin D supplements per day [31].

### Outcome measurements

Primary outcome measures are changes in patients' mobility assessed by the tests described by Guralnik et al [24] and in physical functioning according to the FIM measure [25].

Secondary outcome measures are changes in patients' cognition by verbal flow [17] and MMSE [16], neuropsychiatric symptoms by NPI [21,22] and Cornell [23], number of falls, and permanent institutionalizations and time spent at home. Changes in caregivers' satisfaction, burden by the Zarit burden scale [27], depression by the GDS [28], health-related quality of life by the RAND-36 [29,30] will be measured as secondary outcomes.

Total mortality, use and costs of health and social care services of both spouses as well as cost-effectiveness of the intervention will be measured up to 24 months from the beginning of the baseline measurements.

### Statistical analyses

Sample size was calculated based on the FIM measure [25]. With an estimated standard deviation 20, and type I error 5%, 80% power, 63 patients would be needed in each group to show a 10-point difference between groups. With estimated 10% drop outs in each group about 70 patients are needed in each group. Data will be analyzed on intention-to-treat basis. Imputation method "the last observation carried forward" (LOCF) and "Worst-rank score"-principle will be used.

In these baseline findings, for the continuous variables, descriptive values were expressed by means with standard deviations (SD) and medians with range. For the variables with a normal (Gaussian) distribution, statistical comparisons between the groups are made by using an analysis of variance. If the variables have a non-normal distribution or ordinal level, statistical comparison between groups was made using the Kruskall-Wallis test. Measures with a discrete distribution were expressed as percentages (%) and analysed by Chi-Square or Fischer's exact test when appropriate.

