## Background

Dementia is the most important disease group leading to disability and requiring social and health care among older individuals [1]. The most prevalent of dementing illnesses (55-80%) is Alzheimer's disease which leads to gradual and often steady decline of cognitive functioning, to various behavioural and psychological symptoms and physical disability [2]. Disabilities lead to loss of autonomy, require help and support as well as institutional care. Dementia with its consequences is also very expensive for the society [1].

One pivotal problem in dementia leading to need for help and institutional care is decline in mobility. Locomotion gets stiff, walking decelerates and falls are common [3]. The stiffness and emerging disabilities makes caregivers' work demanding. Going outdoors, getting dressed and undressed as well as transfers from one place to another become challenging [1]. This process is accelerated by patient's progressive sarcopenia, weight loss and muscular weakness which impede body control and predisposes to falls [4].

Some earlier studies have suggested that physical exercise may be beneficial in dementia. Physical activity and regular exercise training may slow down cognitive decline [5,6], and it has positive effects on cognition among those with cognitive decline [7]. Exercise alleviates depression and reduces behavioural symptoms in dementia patients [7,8]. There are several controlled trials testing effectiveness of endurance or strength training among patients with dementia or in samples with a large proportion of patients with dementia. Most of the trials have a low number of participants and, therefore, low power to show effectiveness. In addition, many of the trials are not randomized. A meta-analysis of these trials showed a small but significant effect on strength and endurance outcomes [9]. Majority of these trials have been performed in nursing homes or in long-term care. One randomized study in a nursing home setting has shown that intensive, long-lasting exercise training may even improve physical functioning of Alzheimer's patients [10]. According to the trials showing effectiveness on physical functioning, the training program should be intensive, long-lasting and versatile.

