## Discussion

This trial investigates the effects of intense, long-lasting physical exercise on home-dwelling patients with AD. It has two active intervention arms which are compared with usual care. One third of patients receive home-based tailored exercise twice a week one hour at the time for one year or until the patient is admitted to permanent institutional care. Another third of patients are receiving versatile exercise training including endurance, balance, and strength training as well as dual task training and exercises directed to improve executive functioning. This intervention is provided in day centers for four hours/day twice weekly for one year or until the patient is admitted to permanent institutional care.

There are several strengths in our study. All participants have an established diagnosis of AD because all are recruited from the drug register. This register requires definite diagnosis based on cognitive tests, disability, laboratory tests, and CT scan or MRI scan for the AD drug reimbursement. All participants suffer from frailty, and have therefore a need for exercise rehabilitation. Thus, the findings should be applicable in real life. The exercise training is intense and long-lasting, thus, reinforcing effectiveness of the intervention. The used resources and costs will be counted in detail.

However, there are also several challenges in this study. First, the population is old and frail with many comorbidities, and, thus, vulnerable to competing causes of complications and deaths. The second challenge relates to a sufficient difference to be attained between the groups with our intervention. Contamination of the control group is probably not a problem, because exercise rehabilitation is rarely available for dementia patients in Finland unless they are the Second World War veterans [32], in practice over 83 years of age in 2008. Although the FIM has been developed to measure outcomes of rehabilitation and validated among very old patients [25], it is not very clear how the FIM measure will respond to change in functioning as a consequence of exercise intervention in patients with AD. It was also challenging to find suitable scales to measure change in cognition in this heterogeneous group consisting of all stages of dementia.

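### LOCF is specified for functional outcomes expected to worsen, and a worst-rank rule is named beside it without saying which missing values each one covers

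*Protocol article*

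**What the plan says.** The protocol article, Statistical analyses, sets the analysis principle ("Data will be analyzed on intention-to-treat basis") and then gives one sentence on missing data: "Imputation method 'the last observation carried forward' (LOCF) and 'Worst-rank score'-principle will be used". The sentence ties neither rule to an outcome, a type of patient or a reason for missingness, and sets no order between them.

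It therefore reaches the primary outcomes. The definition in Outcome measurements begins "Primary outcome measures are changes in patients' mobility assessed by the tests described by Guralnik et al [24] and in physical functioning according to the" and closes by naming the scale, which is FIM. According to Study procedures and Table 1, both measures are taken at baseline and at 3, 6 and 12 months, and again at 24 months in patients who still live in the community.

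On the expected course, Background says of Alzheimer's disease: "which leads to gradual and often steady decline of cognitive functioning, to various behavioural and psychological symptoms and physical disability". It also describes worsening mobility. Discussion calls the population "vulnerable to competing causes of complications and deaths".

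The sample size rests on a difference in mean FIM. Its result is "63 patients would be needed in each group to show a 10-point difference between groups", and the allowance for losses is then stated as "With estimated 10% drop outs in each group about 70 patients are needed in each group". The remaining inputs are an SD of 20, a 5% type I error and a power of 80%.

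**The concern.** LOCF assumes that a patient's score would have stayed where it was last seen. Where function is expected to fall, that assumption is wrong in a known direction. On a change score, a patient last seen at baseline is recorded as having no change, and one last seen at 3 or 6 months loses the later part of the decline. The patients most likely to be missing are then counted as more stable than they probably are, and the filled-in value is treated as if it had been observed.

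Two consequences follow. If the arms lose patients equally, a real difference between them is diluted. If they lose patients unequally, the arm with more losses looks better than it is. Unequal loss is conceivable, since one arm attends a centre for four hours twice a week, one is visited at home and one receives usual care. The article does not predict which arm would lose more.

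The worst-rank rule pulls the other way, because it places a patient at the bottom. With no stated assignment, the primary result depends on which rule is applied to whom. Worst ranks also need a rank-based analysis, whereas the sizing rests on a difference in means.

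**Working it through.** **The plan's own figure.** Inputs from Statistical analyses: difference 10, SD 20, type I error 5% (taken as two-sided), power 80%.

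- n per group = 2 × (1.960 + 0.842)² × 20² / 10² = 62.8, so 63. This reproduces.
- With 10% dropout: 63 / 0.90 = 70. This reproduces.

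The sample size is not in question, and a change of imputation rule leaves it as stated.

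**Assumptions that the article does not supply.** It gives no FIM decline rate and no dropout by arm beyond 10% in each. I assume a linear course over 12 months, LOCF applied to every dropout, and a last observation equally likely at 0, 3 or 6 months. The mean share of the year observed is then (0 + 3 + 6) / (3 × 12) = 0.25, so 75% of the change is unseen. The SD is held at 20.

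**Equal dropout p, true difference 10.** LOCF estimate = 10 × (1 − 0.75p).

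- p = 10%: 10 × 0.925 = 9.25. The range is 9.0 if all dropouts were last seen at baseline, to 9.5 if all were last seen at 6 months.
- p = 20%: 10 × 0.85 = 8.5.
- Standard error at 70 per arm = 20 × √(2/70) = 3.38. Power is 84% for 10 points (complete data), 78% for 9.25, and 76% to 80% for 9.0 to 9.5.

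**Unequal dropout, no true effect.** Spurious difference = (p_exercise − p_control) × 0.75 × annual decline. The false-positive rate is two-sided, from this shift divided by 3.38. The last two rows were also simulated with 70 per arm.

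| Dropout, control vs exercise | Assumed decline per year | Spurious difference for exercise | False-positive rate |
|---|---|---|---|
| 10% vs 10% (planned) | any | 0 | 5% |
| 10% vs 15% | 10 | 0.05 × 0.75 × 10 = 0.4 | 5.1% |
| 10% vs 20% | 10 | 0.10 × 0.75 × 10 = 0.75 | 5.6% |
| 10% vs 25% | 10 | 0.15 × 0.75 × 10 = 1.1 | about 6% to 7% |
| 10% vs 30% | 14 | 0.20 × 0.75 × 14 = 2.1 | about 9% to 10% |

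In the 10% vs 25% row, declines of 6 and 14 points give 0.15 × 0.75 × 6 = 0.7 and 0.15 × 0.75 × 14 = 1.6. If the dropout rates are swapped between arms, the sign reverses.

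**Why the assignment matters.** Take no true effect, a 10-point decline in both arms, and dropout of 20% exercise and 10% control.

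- LOCF for all dropouts gives +0.5 to +1.0 (last seen at 6 months to last seen at baseline).
- A worst value assumed to lie 52 to 82 points below baseline gives 0.10 × (10 − 52) = −4.2 to 0.10 × (10 − 82) = −7.2.

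The second figure puts a worst value on the mean scale only to show direction and relative size. It is not what a rank analysis would report.

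**The case against.** A reader might infer that the plan contradicts itself by giving the same patient both a carried-forward value and the worst rank. The text does not support that. It says that both rules will be used, and not that both apply to one patient. Worst-rank for death or inability to be tested, with LOCF for other gaps, is a compatible reading, and the full protocol or analysis plan, which is not shown, may set this out. That part of the objection stands.

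Three further points also have force:

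- The only dropout figure in the article is 10% in each arm. The 25% and 30% figures are hypothetical, and so are the decline rates. At the planned rates and with no effect, LOCF gives no bias, and with a true effect it is conservative.
- If worst-rank takes the deaths, the most informative losses leave LOCF, and the bias calculated for all dropouts no longer applies as shown. Part of the shrinkage is also not bias if patients who stop exercising lose the benefit.
- The steady decline in Background refers to cognition. The same section describes physical disability and worsening mobility, but no FIM slope can be taken from it.

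These points limit the size of the problem and leave its core. LOCF is a method the article states, and so is not detail left to another document. A fuller account of who falls under which rule would not make LOCF sound for an outcome expected to worsen.

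**Conclusion.** The point holds as a should-fix. LOCF is a poor choice for the primary FIM and mobility changes in this population, and the worst-rank rule beside it has no stated scope.

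At the planned 10% dropout in each arm, a true 10-point effect shrinks to about 9.25. Power at 70 per arm is then about 78%, against 84% with complete data and the 80% planned. This rests on an effect that builds up linearly and would have continued after dropout. A spurious gain for exercise needs more dropout there than in control: about 1.1 points in the hypothetical 10% versus 25% case with a 10-point annual decline (0.7 to 1.6 for declines of 6 to 14).

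The documents do not support the stronger conclusion that the primary result is already compromised or that its error rate is inflated. They give neither the decline rate nor the unequal dropout that this would require.

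**What to change.** - Make the primary analysis of FIM and mobility a likelihood-based repeated-measures model on all observed baseline, 3-, 6- and 12-month values, with arm-by-visit and baseline-by-visit terms. Take the 12-month contrast as the result.
- State that worst-rank applies to named events such as death, in a rank-based supporting analysis reported beside the primary one.
- Keep LOCF at most as a labelled sensitivity analysis.

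The cost is a change of wording before the data are analysed. Table 1 already schedules the measurements, and no patients or visits are added. There are two downsides. Intervals may be slightly wider than under LOCF. The model also assumes that data are missing at random, which is doubtful for deaths, and for that reason the worst-rank analysis should be reported alongside it and not dropped.
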